The efficacy of treadmill walking with partial body weight support in non-ambulatory patients after stroke is unclear. A Cochrane Collaboration Systematic Review [9] concludes that there is as yet no definitive answer about whether this intervention helps more non-ambulatory patients learn to walk compared to assisted overground walking. There are randomised controlled trials examining whether treadmill walking and partial body weight support is effective in a mixed group of ambulatory and non-ambulatory patients [7,10-13]. The only RCTs which examine non-ambulatory patients, compare treadmill training and partial body weight support with alternative interventions such as a mechanised gait trainer [14] or aggressive bracing [15] rather than current practice. This situation has led to the Cochrane Collaboration Systematic Review [9] to recommend that separate, large number, high quality studies for non-ambulatory patients be undertaken to examine the efficacy of treadmill walking with partial body weight support after stroke.

The main objective of this randomised controlled trail is to determine whether treadmill walking with partial weight support via an overhead harness is effective at establishing independent walking (i) more often, (ii) earlier and (iii) with a better quality of walking, than current physiotherapy intervention for non-ambulatory stroke patients. The study targets stroke patients who are unable to walk independently on admission to rehabilitation. It will determine the efficacy of treadmill walking with partial weight support via an overhead harness on the establishment and quality of independent walking. Furthermore, by assessing community participation six months later, it will evaluate the longer-term effect of this intervention.

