#### Proportion of participants achieving independent walking

Independent walking will be operationally defined as 'being able to walk 15 m continuously barefoot across flat ground without any aids'. Participants will be tested once a week in the morning (ie, before the training session). Participants will continue to be tested until they achieve independent walking or are discharged.

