#### Quality of independent walking

Quality of walking will be measured by quantifying parameters such as speed, affected and intact step length, step width, and cadence. These parameters are the result of the timing and magnitude of the angular displacements during walking and are therefore global measures which reflect qualitative aspects of walking. When participants achieve independent walking, their overground walking will be measured by placing markers on the heels of both the unaffected and affected legs, so that step length of both the affected and unaffected leg, walking speed, cadence, and step width can be determined.

The 6-month outcome measures will be:

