#### Proportion of participants achieving independent walking

#### Quality of independent walking

#### Community participation

Two aspects of community participation will be measured. First, mobility status will be assessed using the 6-min walk test, number of falls since discharge, a self-efficacy questionnaire about walking capability, and the Adelaide Activities Index. Second, living arrangements will be assessed by recording the type of residence and the amount of support within the residence.

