In addition to, but separate from, the difference in the proportion of participants walking between the groups, there may also be a difference in the quality of walking. On the assumption that 20% of participants may be lost to follow-up and that 80% of participants entering rehabilitation achieve basic independent walking [1], there are likely to be 84 participants with "quality of walking" data at 6 months. Goldie et al [24] has suggested that a minimum difference in walking speed worth detecting is 0.2 m/s. The walking speed of a population of stroke patients who have recently completed rehabilitation [25] on entry to a randomised controlled trial was 0.56 (SD, 0.27) m/s using measurement procedures similar to the present proposal. 60 participants are needed to detect a treatment effect size of 0.2 m/s difference in walking speed between the groups at 6 months with 80% power at a two-tailed significance level of 0.05 therefore 84 participants gives over 90% power.

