### Statistical analysis

The proportion of independent walkers and the time to achieve independent walking will be compared between the two groups using the logrank test, in which those who do not achieve independent walking are censored at the time they are discharged. Survival analysis using Cox's regression will be used to compare the times in the two groups while allowing for possible confounding variables, such as other interventions received, and baseline sitting balance.

The five variables that reflect the quality of walking: speed, affected and intact step length, step width and cadence, will be compared between the two groups using Student's t-test, or Wilcoxon's rank-sum test for variables that are clearly not Normally distributed.

The four variables that reflect the mobility status: 6-min distance, number of falls since discharge, self-efficacy questionnaire about walking capability, and the Adelaide Activities Index will be compared between the two groups using Student's t-test, or Wilcoxon's rank-sum test for variables that are clearly not Normally distributed.

The two variables which reflect living arrangements: type of residence and the amount of support within the residence, will be analysed descriptively.

Descriptive data about lesion, neglect, spasticity and sensation will be used in post-hoc multiple regression analysis to examine if these factors affected walking outcome.

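### Objective (iii), better quality of walking, has no declared deciding gait variable or time, and its initial comparison is tied to a milestone that treatment is meant to move

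*Protocol article*

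**What the plan says.** All references are to the protocol article.

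- **Background.** The main objective is to establish independent walking on three counts: "i) more often, (ii) earlier and (iii) with a better quality of walking". Quality is therefore part of the main objective.
- **Measurement, initial outcomes.** Walking ability is tested weekly: "Participants will continue to be tested until they achieve independent walking or are discharged". Gait is recorded at that milestone: "When participants achieve independent walking, their overground walking will be measured".
- **Measurement, 6-month outcomes.** The list repeats "Quality of independent walking". The end of the Control group section fixes this time point at 6 months after admission to the study.
- **Statistical analysis.** The arms are compared by t-test, or by rank-sum test where a variable is plainly non-Normal, on all of the following: "The five variables that reflect the quality of walking: speed, affected and intact step length, step width and cadence". This section gives no lead variable, lead time, order of testing or significance level.
- **Sample size.** Quality is powered on one variable at one time, walking speed at 6 months, on the basis that "a minimum difference in walking speed worth detecting is 0.2 m/s". The section states that 60 participants give 80% power at two-tailed 0.05, and that the expected 84 give over 90%.

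**The concern.** The sample size rests on one comparison, but the analysis text treats five variables at two occasions, ten comparisons in all, as equals. A reader of the results could not tell which of them settles objective (iii). If a favourable result on any one were accepted, the false-positive risk for a limb of the main objective would exceed 5%.

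The initial gait comparison has a separate weakness. Each patient is measured on reaching independent walking, and objective (ii) hopes that treatment brings this forward. If it does, the arms are compared at different times since stroke, and a gait difference at that point cannot be separated from the effect on time to walking. The 6-month measurement does not share this problem, because it is anchored to study admission.

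**Working it through.** **1. The plan's own figures.** Inputs from Sample size: difference 0.2 m/s, SD 0.27 m/s, two-sided 0.05, 80% power, equal allocation.

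- Per arm: n = 2 × (1.960 + 0.842)² × 0.27² / 0.2² = 28.6, so 29 per arm or 58 in total. The t-test calculation gives 29.6, so 30 per arm or 60 in total, as stated.
- Expected participants with data: 130 × 0.8 × 0.8 = 83.2, against the stated 84.
- Power with 42 per arm: 0.2 / (0.27 × √(2/42)) = 3.39, and Φ(3.39 − 1.96) = 92.4% (t-test 91.8%). The stated figure of over 90% is reproduced.

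**2. False-positive risk with no deciding test.** Two assumptions are needed: every comparison is run at two-sided 0.05, the only level the article gives (in Sample size), and any significant result is read as better quality.

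- Five independent tests: 1 − 0.95⁵ = 22.6%.
- Ten independent tests: 1 − 0.95¹⁰ = 40.1%.

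These are ceilings. Speed depends on step length and cadence, and the same people are measured twice. The document gives no correlations, so a range was simulated (400,000 replicates per setting, normal test statistics):

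| Tests | Assumed correlation | Chance of at least one false positive |
|---|---|---|
| 5 (one time) | 0.3 between variables | 21.0% |
| 5 | 0.5 | 18.3% |
| 5 | 0.7 | 14.9% |
| 5 | 0.9 | 10.2% |
| 10 (two times) | 0.3 between variables, 0.5 between times | 35.2% |
| 10 | 0.5 and 0.5 | 31.2% |
| 10 | 0.7 and 0.8 | 22.1% |

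**3. What each remedy costs in power for speed with 84 participants.**

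| Approach | Level for speed | Power (normal / t-test) | Total needed for 80% power (normal) |
|---|---|---|---|
| Speed at 6 months alone | 0.05 | 92.4% / 91.8% | 58 |
| Bonferroni over five | 0.01 | 79.4% / 77.3% | 86 |
| Bonferroni over ten | 0.005 | 72.2% / 69.3% | 98 |

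**4. Timing of the initial measurement.** The design target is 50% versus 75% walking by six weeks. With constant hazards, assumed for illustration only, 50% by six weeks means a median of 6 weeks. Since 75% by six weeks is two successive halvings of those not yet walking, the other median is 6 / 2 = 3 weeks. If the trial met its own target, the medians would differ by about three weeks. Censoring at discharge would narrow the gap among those actually measured. The calculation shows that unequal timing follows from the schedule. It does not show which arm benefits.

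**The case against.** The strongest reply is that an article may leave decision rules and multiplicity adjustment to a full protocol or analysis plan, and that Sample size already singles out speed at 6 months, with one minimum difference and one level. That stands in part. Silence on adjustment is not in itself a fault, and an implicit lead variable exists. But the article sets out the variables, occasions, tests and power basis for a limb of its main objective, and the powered comparison is never declared the deciding one.

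A reader might go further in three ways that the document does not support.

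- **That the trial will test each variable at 0.05 and claim success on any of ten.** Statistical analysis gives no level and no such rule. Both are conditions of the calculation.
- **That the false-positive risk is 40%.** That needs ten independent tests, which these variables cannot supply.
- **That at first walking everyone sits near a threshold, so the comparison works against the arm that walks earlier.** The milestone is 15 m continuously, barefoot and without aids. It sets no criterion for speed, step length, step width or cadence. Earlier walkers may also be less severely affected, which would push the other way.

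It is also fair to say that measuring quality when walking is established matches the wording of the objective. That is a reason to keep and report the measurement, but it does not remove the confounding with time to walking.

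**Conclusion.** The point holds as a mismatch between what was powered and what is analysed. Objective (iii) rests on five gait variables at two occasions with none declared as deciding, while only speed at 6 months has a power calculation, and that calculation reproduces. Under the two stated assumptions the false-positive risk is about 10–21% for five tests and 22–35% for ten. These ranges rest on assumed correlations.

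The initial gait comparison is made at unequal time since stroke and is confounded with any effect on time to walking; the direction of bias cannot be fixed from the document. The timing problem does not extend to the 6-month measurement.

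This is a cheap improvement that changes what the trial can conclude about objective (iii). It does not threaten the comparison of the proportion walking or of time to walking.

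**What to change.** - In Statistical analysis, name walking speed at 6 months as the single deciding comparison for objective (iii), at two-sided 0.05. This holds the error for that objective at 5%.
- Report the other four gait variables at 6 months, and all gait measures at first independent walking, as supportive: estimates with confidence intervals and no claim of efficacy. Note that the measures at first walking are taken at unequal time since stroke.
- State that the 6-month speed comparison is conditional on walking and on being followed up. It covers about 84 of 130 participants, a group defined after randomisation whose size the treatment is meant to change. It must therefore be read alongside the proportion walking in each arm. Naming a deciding variable does not remove this selection.

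**Cost.** Wording only: no added participants, visits or measurements. The downside is that a benefit confined to step length, step width or cadence becomes supportive evidence only.

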### Randomization

Participants will be randomised into an experimental or a control group. We will stratify the randomisation. First, given the potential confounder of site, participants at each site will be randomised separately. Second, at each site, participants will be stratified according to initial level of motor disability since it has been found to affect outcome [16]. Since all the participants will be unable to walk on admission to the study, sitting balance will be used to stratify the allocation of participants to groups because it has been found to be a useful prognostic indicator of walking outcome [17-19]. Therefore, participants will be stratified according to Item 3 (Sitting Balance) of the Motor Assessment Scale for stroke [20] so that those with a score of 0–3 will be classified as severely disabled and those with a score of 4–6 will be classified as moderately disabled. Within each of the two strata (moderate versus severe level of disability), participants will be allocated randomly to one of two groups, the experimental group or the control group. Random permuted blocks will be used so that after every block (of 6–10 participants), the experimental and control groups will contain equal numbers. In summary, stratification will occur according to site (three sites) and level of disability (two levels). Therefore, there will be 6 strata and participants will be randomised separately within each stratum. The random sequence of group allocation will be concealed from the person recruiting participants.

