### Sample size

130 participants will be recruited. The sample size has been calculated to reliably detect a treatment effect size of a 25% increase in proportion of independent walkers with 80% power at a two-tailed significance level of 0.05. For non-ambulatory patients, it takes an average of 3 months to achieve independent walking with about 50% walking independently at six weeks [1]. We are interested in being able to detect a 25% increase, from 50% to 75%, proportion of non-ambulatory patients walking independently by six weeks. Only an effect such as this is clinically significant enough to warrant a change in the implementation of services which would involve the re-education of physiotherapists and the expense of purchasing a treadmill and overhead harness system. The smallest number of participants to detect this difference between two proportions estimated from independent samples is 65 participants per group, ie, 130 participants in total [23]. However, since the analysis of the data is survival curve analysis, there is greater power than the calculation would suggest because the effect of dropouts is minimal in this analysis. For example, in a pre-post design trial of 6 weeks intervention, if a subject dies or is lost to follow-up (ie, drops out) at 5 weeks, there is no measurement at the post-test on which to perform an analysis. In this trial, which ascertains once a week whether independent walking has been established, they would be censored at five weeks so that they no longer form part of the total sample. However, this participant's data would be available for the five weeks they participated in the trial thereby minimising the effect of their dropping out.

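### Student's t-test on gait measured only in walkers gives a slightly wrong standard error if the arms differ in both walker numbers and SD; Welch's test avoids this at almost no cost

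*Protocol article*

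**What the plan says.** - **Test.** Under Statistical analysis, speed, the two step lengths, cadence and step width "will be compared between the two groups using Student's t-test, or Wilcoxon's rank-sum test for variables that are clearly not Normally distributed". Student's test in its usual meaning pools the two variances. No unequal-variance form is named.
- **Who is measured.** Under Measurement, gait is recorded once a participant can walk independently, and again at 6 months. Non-walkers supply no gait data.
- **Planned effect.** Under Sample size, the trial is sized for a change "from 50% to 75%, proportion of non-ambulatory patients walking independently by six weeks", with "65 participants per group, ie, 130 participants in total".
- **Speed.** The same section says "a minimum difference in walking speed worth detecting is 0.2 m/s" and that "60 participants are needed to detect a treatment effect size of 0.2 m/s difference in walking speed between the groups". That calculation concerns the 6-month comparison and aims for 80% power at a two-sided level of 0.05. It uses a single SD of 0.27 m/s around a mean of 0.56 m/s, 20% loss to follow-up and one overall walking rate of 80%, not split by arm.
- **Allocation.** Under Randomization, after each block "the experimental and control groups will contain equal numbers".

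**The concern.** Student's test tolerates unequal SDs when the groups are the same size. Randomisation provides that for outcomes measured in everyone, but gait is measured only in walkers. If treatment makes more people walk, the gait groups are unequal because the treatment worked. The pooled standard error then leans towards the SD of the larger group, and the interval is too wide or too narrow depending on which arm varies more.

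At stake are the accuracy of the confidence intervals and some power for the third part of the main objective (better quality of walking), chiefly for speed, the one gait variable with a power calculation.

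**Working it through.** **1. The plan's own figure.** With a difference of 0.2 m/s, SD 0.27 and two-sided 0.05, the noncentral t calculation gives 29.6, so 30 per arm or 60 in total for 80% power, as stated. Expected gait data: 130 × 0.8 × 0.8 = 83.2 (stated as 84). At 42 v 42 the power is 91.8%, which agrees with the stated figure of over 90%. The calculation assumes equal groups and equal SDs.

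**2. Walker numbers under the planned effect.**
- Six weeks: 65 × 0.50 = 32.5 and 65 × 0.75 = 48.75, taken as 32 v 49.
- 6 months: 65 × 0.8 = 52 followed per arm. The article gives no split by arm. *Assuming* a 25-point gap centred on 80%: 52 × 0.675 = 35.1 and 52 × 0.925 = 48.1, taken as 35 v 48.

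**3. Unequal numbers alone.** With equal SDs, the simulated level of Student's test is 4.9% at 32 v 49 and 5.0% at 35 v 48. Power for 0.2 m/s is 89.6% and 90.9%. No harm follows.

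**4. Unequal numbers and unequal SDs.** *Assume* SD is proportional to mean speed: 0.27 × 0.76/0.56 = 0.366 in the arm that gains 0.2 m/s. The formulas are:
- pooled variance = [(n1−1)s1² + (n2−1)s2²]/(n1+n2−2)
- pooled SE = √[pooled variance × (1/n1 + 1/n2)]
- correct SE = √(s1²/n1 + s2²/n2)

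*Larger group more variable (s1 = 0.27, s2 = 0.366):*
- 32 v 49: pooled variance (31×0.0729 + 48×0.1343)/79 = 0.1102; pooled SE 0.0755, correct SE 0.0708, so 6.5% too large.
- 35 v 48: pooled variance (34×0.0729 + 47×0.1343)/81 = 0.1085; pooled SE 0.0732, correct SE 0.0699, so 4.8% too large.
- Simulated power for 0.2 m/s, Student v Welch: 75.9% v 79.6% at 32 v 49, and 78.3% v 81.0% at 35 v 48.

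*Smaller group more variable (SDs swapped):*
- Pooled SE 0.0708 against 0.0754 at 32 v 49 (6.1% too small), and 0.0698 against 0.0732 at 35 v 48 (4.6% too small).
- The simulated level of Student's test is about 6 to 6.5%.

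**5. Wider range of SD ratios.** True level of Student's test at nominal 5%, Normal data, 40,000 runs per cell. The experimental arm is the larger group.

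| SD ratio, experimental/control | 32 v 49 | 35 v 48 |
|---|---|---|
| 0.5 | 8.4% | 7.4% |
| 0.67 | 7.1% | 6.4% |
| 0.8 | 5.9% | 5.8% |
| 1 | 4.9% | 5.0% |
| 1.25 | 3.9% | 4.3% |
| 1.5 | 3.4% | 3.8% |
| 2 | 2.7% | 3.2% |

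Welch's test stayed at 4.8 to 5.2% in every cell. With equal SDs it cost about 0.2 points of power.

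**6. Equal groups.** With n per arm the two SE formulas coincide, both equal to √[(s1² + s2²)/n]. At 42 v 42 and 52 v 52 Student's test kept 4.9 to 5.2% at every SD ratio tried.

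**The case against.** The case against has real force.

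- **Unequal SDs are not in the document.** It gives one SD. This stands: every ratio above 1 or below 1 is an assumption.
- **The natural argument for unequal SDs points in the safe direction.** If SD follows the mean, then with no speed difference the SDs are equal and the level stays at 5%. With a speed gain, the treated arm is both larger and more variable, so Student's interval is conservative (96.0% coverage at 35 v 48). This stands. A reader might infer that the 5% level is at risk of inflation, but that needs the smaller group to be the more variable one, and nothing in the article suggests it. The cost in the more plausible case is lost power.
- **The 50% and 75% rates are for six weeks, while speed is powered at 6 months.** This stands. The two should not be combined with the 20% loss to give 26 v 39 walkers, because that total of 65 conflicts with the 84 expected at 6 months. The 35 v 48 split respects the article's total but still assumes the gap.
- **The mobility variables.** The same test is planned for them, and a reader might extend the point to them. The article does not restrict these measures to walkers, so groups of about 52 v 52 are expected and pooling does no harm.
- **Choosing between t and rank-sum from the data.** A reader might suspect that this inflates error. Simulating a mechanical rule gave 4.9 to 5.2%, and the article has the data analysed by a researcher blinded to allocation. The missing criterion for non-Normality is detail that an analysis plan commonly supplies. Nor does a rank test rule out an estimate in m/s, since the Hodges-Lehmann shift is one.

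What survives is that the article names a specific test, the trial's own target effect removes the equal group sizes that make that test robust, and a better one is almost free.

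**Conclusion.** The point holds as a minor one, for the five gait variables only. It needs two conditions together: more walkers in one arm, which the planned effect implies, and different SDs, which the article neither states nor excludes. With SDs of 0.27 v 0.366 and the faster, larger arm more variable, Student's standard error is 4.8% to 6.5% too large and about 3 to 4 points of power are lost. With the SDs reversed, the level is about 6 to 6.5%. With equal SDs there is no error. The 6-month split rests on an assumed 25-point gap.

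A separate and larger matter remains. Gait is compared among people selected after randomisation by an outcome that treatment may change. The choice between Student's and Welch's test does nothing for that.

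**What to change.** In Statistical analysis, for speed, both step lengths, step width and cadence, replace Student's t-test with Welch's t-test, or with a linear model with robust standard errors that adjusts for the randomisation strata (site and sitting-balance level). For speed, state in advance that the estimate is the difference in means in m/s with a 95% CI, so that it matches the 0.2 m/s used under Sample size. Keep the rank-sum test as a named sensitivity analysis. The mobility variables need no change on this account.

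The cost is a change of wording, with no extra participants or data. With equal SDs Welch's test gives up about 0.2 points of power. For strongly skewed variables, a comparison of means has less power than a rank test.

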### Intervention

Both the experimental and the control group will undergo a maximum of 30 minutes per day of walking practice with assistance from one therapist, five days a week until they walk or until discharge from rehabilitation. The total daily time of intervention will be 30 minutes from beginning (ie, from when the participant is in the gym) to end (ie, when the participant is back in the wheelchair). This time therefore includes transferring, putting on aids or setting up equipment, ie, training does not have to be continuous so that rests may be taken. The amount of assistance during walking will be standardised to one therapist, however, additional help will be allowed during setting up walking (ie, getting the participant onto the treadmill for treadmill walking or into standing for overground walking). The rationale for this protocol is based on clinical observation of how much time and how many therapists are currently used in trying to get a non-ambulatory person to walk. Other intervention involving lower limb function, (ie, strengthening exercises, practice loading the affected leg during activities such as sitting, standing up and standing) will be standardised to 60 min per day. No other part of the multidisciplinary rehabilitation program will be controlled. Randomization should ensure that any effect of other interventions will be the same for both groups, therefore, other therapies will not be withheld.

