#### Control group

Training for the *control *group will involve current practice of assisted overground walking. If a participant is too disabled to walk with the help of one therapist, they will practise stepping forwards and backwards or standing with a knee splint and practising shifting weight from leg to leg. Aids such as knee splints, ankle-foot orthoses, parallel bars, forearm support frames and walking sticks can be utilised as part of training. Training aims to produce independent walking. Therefore, progression of training encompasses both increasing speed and reducing assistance from both aids and the therapist. Information describing the specific features of the training session (such as use of aids, distance walked, assistance required) will be recorded to monitor adherence to the guidelines and to be able to describe the intervention accurately.

The end-point of the training phase of the study will be either the attainment of independent walking or discharge from the rehabilitation unit. The end-point of the follow-up phase of the study will be 6 months after admission to the study.

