## Discussion

Australia, like many other developed nations, is undergoing a major demographic shift involving significant growth in the aged population. The Australian Government has recognised that a revolution is underway at the end of the life cycle. In its National Research Priorities, the Government has recognised that it will be important to promote healthy ageing and that this endeavour will be underpinned by research. Only by establishing evidence-based interventions, such as the one outlined in this project, will the severity of many health problems be reduced. In economic terms, if non-ambulatory patients do not learn to walk after their stroke, it is likely that they will require assisted care, placing a high burden on the community. Furthermore, given that independence in walking is a major factor in the decision to discharge patients from inpatient care, earlier independent walking should result in a reduction in length of hospital stay which should result in cost saving. The Queensland Health Report "Hospital benchmarking pricing model" has estimated the cost of a day in hospital for a neurological patient at $880. In summary, this study has the potential to reduce disability following stroke by improving the outcome of walking and thereby to reduce the burden of this condition on the community. Increasing the number of people who can walk after stroke should reduce the demand for nursing home placement.

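### Falls after discharge are compared as raw counts, so if length of stay differs between arms the comparison is distorted against the arm discharged earlier

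*Protocol article*

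**What the plan says.** Four statements in the protocol article, read together, define the falls comparison.

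- **Start of counting.** Under Community participation, "mobility status will be assessed using the 6-min walk test, number of falls since discharge". The clock starts at discharge.
- **End of counting.** Under Control group, "The end-point of the follow-up phase of the study will be 6 months after admission to the study". The end is tied to study entry, not to discharge.
- **Discharge is not fixed.** Under Intervention, training runs "five days a week until they walk or until discharge from rehabilitation". No length of stay is set.
- **Test.** Under Statistical analysis, the mobility variables include "6-min distance, number of falls since discharge, self-efficacy questionnaire about walking capability", and all of them "will be compared between the two groups using Student's t-test, or Wilcoxon's rank-sum test for variables that are clearly not Normally distributed". No rate, offset or person-time is mentioned.

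Two further statements bear on whether stay could differ between arms. The Background asks whether the treatment is "effective at establishing independent walking (i) more often, (ii) earlier" than current practice. The Discussion says that "independence in walking is a major factor in the decision to discharge patients from inpatient care", and that "earlier independent walking should result in a reduction in length of hospital stay".

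**The concern.** A count over unequal periods mixes how often people fall with how long they were observed. In this trial the period of observation could depend on the treatment. If earlier walking leads to earlier discharge, participants in the arm that walks sooner spend more of the six months in the counting window. With the same underlying fall rate in both arms, that arm would record more falls, and a nominal 5% test would reject too often. A treatment that works as hoped could then be reported as increasing falls.

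**Working it through.** The protocol states no figure for falls, so there is none to reproduce. The check is on time at risk and on how the two named tests behave.

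**Inputs from the protocol**
- Window: discharge to six months after study entry, taken as 26 weeks.
- Participants: 130, with 20% assumed lost by six months (Sample size). 130 × 0.8 = 104, or 52 per arm.
- Tests: t-test or rank-sum test on the number of falls.

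**Assumptions, because the protocol gives neither stay nor fall rate**
- Mean stay 12 weeks in the control arm, and 12, 10 or 8 weeks in the experimental arm, SD 3 weeks.
- The same true rate in both arms: 1, 2 or 4 falls per person-year.
- Counts either Poisson or overdispersed (gamma variation between people with variance 1).

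**Formulas**
- Time at risk = 26 − length of stay, in weeks.
- Expected falls = annual rate × time at risk / 52.
- At equal rates, the ratio of expected falls equals the ratio of times at risk.

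**Results**

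Expected falls are shown at 2 per person-year. The last column is the range of simulated type I error over all rates, both levels of dispersion and both tests (3,000 replicates per scenario, 52 per arm).

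| Stay, control vs experimental (weeks) | Time at risk (weeks) | Ratio | Expected falls per person | Type I error at nominal 0.05 |
|---|---|---|---|---|
| 12 vs 12 | 14 vs 14 | 1.00 | 0.54 vs 0.54 | 0.043–0.056 |
| 12 vs 10 | 14 vs 16 | 16/14 = 1.143 | 0.54 vs 0.62 | 0.065–0.107 |
| 12 vs 8 | 14 vs 18 | 18/14 = 1.286 | 0.54 vs 0.69 | 0.081–0.281 |

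For example, 2 × 14/52 = 0.54 and 2 × 18/52 = 0.69.

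The top of each range comes from Poisson counts at 4 falls per year. Overdispersion lowers the error rate but leaves the ratio of expected counts unchanged. The t-test and the rank-sum test behave alike (0.281 and 0.270 in the worst 4-week case), so moving to the rank-sum test for non-Normal data does not help. With equal stays both tests hold their level. A comparison per person-time takes exposure out, so its expected rate ratio is 1.00 when true rates are equal; the rate model itself was not simulated.

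**The case against.** **No bias unless stays differ.** A reader might infer that the experimental arm has longer exposure by design. The documents do not support that. Nothing in the design makes stays differ. The Discussion states an expectation, and calls walking a major factor in discharge, not the only one. If the treatment does not change discharge, randomisation gives equal average exposure. This objection stands, and the point is conditional.

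**The size is assumed.** This also stands. One could assume stay is halved, 12 to 6 weeks, which gives 20/14 = 1.43, but no passage supports so large a shift.

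**The rank-sum test deals with skewed counts.** It does, so a complaint that a t-test suits counts with many zeros poorly is already met. It does not deal with exposure.

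**Falls as a safety outcome.** A reader might infer that falls are the trial's safety endpoint and rate the problem higher for that reason. The article lists them as one of four mobility measures under community participation and does not call them a safety outcome. A condensed article's silence on safety is not a finding.

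**Total falls in the community by six months may be of interest.** Earlier discharge would then be part of the treatment's effect. This is the strongest argument for keeping the raw count, but the protocol does not state that aim. The count also leaves out falls before discharge, so it is not total falls over six months either. It can be reported descriptively.

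**A later analysis plan might adjust.** It could, but the article names both the variable and the test, so that plan would have to replace stated text.

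**Conclusion.** The point holds in conditional form. The protocol fixes a comparison of raw fall counts over a window whose length depends on discharge, and neither named test corrects for that. If the arms have the same stay, there is no bias. If the treatment shortens stay, as the Discussion expects, the arm discharged earlier shows more falls at an equal rate: about 14% to 29% more for stays 2 to 4 weeks below an assumed 12 weeks. Confidence is high in the mechanism. Whether bias will occur, and how large it will be, depends on stays and fall rates that the protocol does not give.

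The reach is limited to one of four mobility variables at six months. The logrank comparison of walking, the sample size of 130 and the walking-speed power calculation are untouched.

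**What to change.** Replace the test for falls with a comparison per person-time. Suggested wording: *Falls after discharge will be compared as rates by negative binomial regression, with log(days from discharge to the 6-month assessment or death) as offset; the rate ratio will be reported with its 95% CI. Participants not discharged by six months contribute no exposure and will be reported separately.* The raw count can remain as a descriptive summary. Counting falls over a window of the same length in every participant is an alternative.

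The cost is about one line of analysis text and a recorded discharge date for everyone. The main analysis needs that date only for those who do not walk, because they are censored at discharge, but a count of falls from discharge already presupposes it for all. No extra visits or participants are needed. The small downside is that the offset assumes falls accrue in proportion to time since discharge, which the documents do not establish.
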